**(2) Exclusion criteria**

1. Persons with alcohol intolerance
2. Have a history of antimicrobial use within the past 4 weeks from the time of study entry
3. Those taking drugs with side effects of diarrhea or constipation.
4. Other persons who are judged by a physician to be unsuitable for the subject.

**5. Target number and study period**

**(1) Target number**

Overall target number of cases eight

**(2) Research period**

Research period: Date of approval - March 31, 2023

Registration period: Date of approval - January 31, 2022

Observation period (follow-up period): 3 months after the end of enrollment

Analysis period: Date of approval - March 31, 2023

**6. Research methods**

**(1) Study design**

Single arm (2 doses) before/after study (single center)

**(2) Research Methods**

**Recruitment of research participants**

Kanazawa University staff will be notified via bulletin boards and mailing lists within 　Kanazawa University, and participants, including family members of staff, will be invited (excluding those involved in this study and their families).

**Allocation of research subjects**

The principal investigator will assign the amount and duration of sake-kasu intake to the research subjects. The amount and duration of intake of sake lees will be assigned in numerical order for each subject enrolled in the study.

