**Objective**

The study described in this research protocol (hereafter referred to as "this study") is a pilot study aimed at evaluating changes in metabolites and bacterial flora in stools by amount and duration of sake-kasu intake in patients with chronic constipation. Based on the results obtained in this study, the amount and duration of sake lees intake in a small randomized controlled trial (RCT) in patients with chronic kidney disease (CKD) will be established.

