**Research Procedures**

1. Provide nutritional guidance prior to intervention using our own sake-kasu recipe (Attachment 1).
2. Sake lees 25 g/day or sake lees 50 g/day for 6 weeks
3. Sakekasu (sake lees) from "Kakuma-no-sato", a refined sake sold by Kanazawa University, will be used. The same lot of sakekasu will be provided to the participants free of charge in order to ensure the same conditions for the intervention.
4. Store sake lees in a refrigerator at about 5℃.
5. Participants can choose how to cook sake-kasu from a collection of sake-kasu recipes
6. Outcome items will be assessed at intervention, 2, 4, and 6 weeks
7. The intake of sake lees and defecation should be recorded daily on the record sheet.
8. The timing and frequency of sakekasu intake is not set. For example, 25 g of sakekasu can be consumed in one meal or divided into three meals.
9. During the introduction period (2 weeks) and the intervention period (6 weeks), the consumption of lactic acid bacteria preparations, foods for specified health uses and foods with functional claims that improve the intestinal environment is prohibited. (Fermented foods other than sake lees, such as miso and yogurt (general foods), may be consumed.
10. The same dinner (a frozen home-delivered lunch with controlled nutritional value) on the day before the evaluation
11. Breakfast on the day of evaluation after 2, 4, and 6 weeks will be the same meal containing sakekasu

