**10. Statistical matters**

**Number of cases design**

Eight cases were set based on feasibility.

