**13. Procedures for obtaining informed consent**

The principal investigator or a co-investigator will give the research subjects a written explanation of consent that has been approved in advance by the Ethics Review Committee, provide sufficient explanation in writing and orally, and obtain consent in writing from the research subjects to participate in the research of their own free will as to whether or not they will participate in the research. This research will not involve persons who need to give their consent in lieu of others or persons under 16 years of age.

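### Intake amount is assigned by the principal investigator in enrolment-number order with no stated randomisation or concealment, which exposes the 25 g versus 50 g contrast to selection bias

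*Protocol*

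**What the plan says.** The allocation text in section 6(2) has two sentences. The first names the allocator: "The principal investigator will assign the amount and duration of sake-kasu intake to the research subjects". The second gives the rule: "The amount and duration of intake of sake lees will be assigned in numerical order for each subject enrolled in the study". It does not say whether the two amounts alternate or run in blocks, how many participants receive each, or when assignment happens relative to consent or baseline sampling. No section mentions randomisation, a concealed list, an independent allocator or blinding.

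On consent, section 13 says: "The principal investigator or a co-investigator will give the research subjects a written explanation of consent". The person who assigns may therefore also be the person who enrols.

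The Objective in section 2 is a comparison by amount: "evaluating changes in metabolites and bacterial flora in stools by amount and duration of sake-kasu intake in patients with chronic constipation". It adds that from the results "the amount and duration of sake lees intake in a small randomized controlled trial (RCT) in patients with chronic kidney disease (CKD) will be established". The design rationale in section 3 repeats this use. The number of participants is fixed in section 10: "Eight cases were set based on feasibility".

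On duration, the Research Procedures in section 6(2) say: "Sake lees 25 g/day or sake lees 50 g/day for 6 weeks". Section 3 also gives 6 weeks to everyone.

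**The concern.** The study has no comparator, so the contrast between the two amounts is its only concurrent comparison, and choosing an amount for the next trial requires looking at it, formally or not. When the person enrolling can foresee the next amount, the decision to enrol, or when to enrol, can depend on it. The protocol leaves room for this: the last exclusion criterion is an open physician judgement, eligibility needs any two of six largely self-reported symptoms, and recruitment is among university staff and their families. The two groups could then differ in severity, motivation, diet or adherence for reasons unrelated to the amount.

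A second issue depends on how the order is read. If one amount is completed before the other starts, amount also tracks enrolment time. With staggered enrolment it would then track the storage age of the single refrigerated lot of sake lees as well.

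**Working it through.** **Inputs.** Total N = 8 and two amounts, 25 and 50 g/day (sections 5, 6 and 10). The split is not stated; 4:4 is assumed. The plan gives no power calculation or dose-contrast figure to reproduce.

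**1. Predictability.** Under any fixed order known to the allocator, 8 of 8 assignments are predictable. Under a concealed random 4:4 list there are C(8,4) = 70 equally likely sequences. Someone who sees past assignments and always guesses the amount with more places left expects 4 + 2⁷/70 − 0.5 = 5.33 correct guesses, or 5.33/8 = 67%. The fair comparison is therefore 100% against 67%, not 100% against 50%.

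**2. Link between amount and enrolment order.** Number the participants 1 to 8, with 25 g first. The gap is the mean position on 50 g minus the mean position on 25 g. The positions have SD √((8² − 1)/12) = √5.25 = 2.291, so with equal groups the correlation of order with amount is gap × 0.5/2.291.

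| Order | Mean positions (50 g; 25 g) | Gap | Correlation |
|---|---|---|---|
| Alternating | 5; 4 | 1.0 | 0.22 |
| Consecutive blocks | 6.5; 2.5 | 4.0 (the maximum) | 0.87 |
| Random 4:4, over 70 sequences | – | mean 0, SD 1.73 | mean 0 |

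A single random sequence can still be unbalanced (SD 1.73 positions), but neither the enroller's choices nor the order of arrival determines it.

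**3. Weight of one participant.** With 4 per amount, one steered participant is 1/4 = 25% of a group. With a 3:5 split it would be 1/3 = 33% of the smaller group.

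**4. Precision of the dose contrast in any case.** The 95% half-width is t(0.975, 6 df) × √(1/n₁ + 1/n₂) in SD units. For 4:4 this is 2.447 × √0.5 = 1.73 SD; for 3:5 it is 2.447 × √0.533 = 1.79 SD. Power for a true difference of 1 SD at 4:4, by the normal approximation, is Φ(1/√0.5 − 1.96) = Φ(−0.546) = 29%.

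**5. What the primary analysis uses.** Section 3 takes the pre-intervention state as the control, section 9 defines the endpoint as percent change, and the data analysis text in section 6(2) plans a before/after comparison by analysis of variance and Dunnett's test. No between-amount test is named. Each participant serves as their own control, so the validity of that test does not depend on how amounts were assigned. Likewise, duration is judged from weeks 2, 4 and 6 within participants.

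**The case against.** The strongest reply is that this is declared a single-arm before/after pilot, sized on feasibility, with no planned test between amounts. That is right as far as it goes: the primary comparison is not touched, and a reader who inferred that the allocation rule undermines the primary result would go beyond the documents. What remains is that the Objective itself asks for results by amount and uses them to set the next trial's intake.

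A reader might also infer that the next amount is always known, or that amount is fully confounded with calendar time and storage age. The text supports neither as fact. Enrolment-number order could mean alternation, blocks or a prepared numbered list. Predictability is a strong inference, because no list or concealment is described, but it remains an inference. Near-complete confounding with time needs the block reading; under alternation the gap is one position. The approval date and pace of enrolment are not shown, so the calendar spread is unknown, and eight volunteers could start almost together.

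The outcome is a laboratory concentration referred to each participant's own baseline, and constipation quality of life, diet and body composition are recorded at or before the start. This partly offsets baseline differences and makes some imbalance visible. It does not correct for later differences in motivation, adherence or background diet.

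Finally, eight participants give an imprecise contrast however they are allocated. That is true, but imprecision shows in the interval, whereas selection does not.

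**Conclusion.** The point holds for the dose contrast and not for the primary before/after analysis. As written, allocation is non-random, made by someone who may also obtain consent, and tied to enrolment number. The next amount is probably predictable, and the 25 g versus 50 g comparison that informs the later trial is open to selection bias. The percent-change endpoint offsets this only in part.

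The size of any bias cannot be computed from the documents, and there is no evidence that steering would occur. The figures describe exposure only: 8 of 8 predictable under a known fixed order against 67% under a concealed random 4:4 list, and an enrolment-position gap of 1 (alternation) or 4 (blocks). The 67% and the gap of 1 rest on the assumed 4:4 split. Even when properly allocated, the contrast remains very imprecise, at about ±1.73 SD.

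The per-subject assignment of duration against 6 weeks for everyone is a separate contradiction. It adds nothing to the case on selection bias.

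**What to change.** Replace the second sentence of the allocation text with wording to this effect: the two existing intake amounts are allocated by a computer-generated random list (4:4 if equal groups are intended; state the split), held by an existing staff member not involved in recruitment, and revealed for each participant only after consent and confirmed eligibility. Preferably the amount is revealed after the baseline samples at visit 2. Because section 12(2) indicates that sake lees is delivered to participants' addresses, it may be revealed before that sampling only if delivery requires it, and the text should say so.

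State that the comparison between amounts is exploratory, and report it with its interval.

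Separately, reconcile the allocation text, which has duration assigned per subject, with section 3 and the Research Procedures, which give 6 weeks to everyone.

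The cost is a short amendment, one list and minor delivery logistics, with no extra participants, visits or assays. It has to be done before the first assignment, because concealment cannot be restored afterwards.

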**Research Procedures**

1. Provide nutritional guidance prior to intervention using our own sake-kasu recipe (Attachment 1).
2. Sake lees 25 g/day or sake lees 50 g/day for 6 weeks
3. Sakekasu (sake lees) from "Kakuma-no-sato", a refined sake sold by Kanazawa University, will be used. The same lot of sakekasu will be provided to the participants free of charge in order to ensure the same conditions for the intervention.
4. Store sake lees in a refrigerator at about 5℃.
5. Participants can choose how to cook sake-kasu from a collection of sake-kasu recipes
6. Outcome items will be assessed at intervention, 2, 4, and 6 weeks
7. The intake of sake lees and defecation should be recorded daily on the record sheet.
8. The timing and frequency of sakekasu intake is not set. For example, 25 g of sakekasu can be consumed in one meal or divided into three meals.
9. During the introduction period (2 weeks) and the intervention period (6 weeks), the consumption of lactic acid bacteria preparations, foods for specified health uses and foods with functional claims that improve the intestinal environment is prohibited. (Fermented foods other than sake lees, such as miso and yogurt (general foods), may be consumed.
10. The same dinner (a frozen home-delivered lunch with controlled nutritional value) on the day before the evaluation
11. Breakfast on the day of evaluation after 2, 4, and 6 weeks will be the same meal containing sakekasu

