D-serine and D-alanine, a type of D-amino acid, have been confirmed to have renoprotective effects by research members^9)^ . Fermented foods such as sake-kasu contain D-amino acids, and direct intake of D-amino acids from sake-kasu may provide renoprotective effects. However, there are no studies that have examined changes in D-serine and D-alanine in stool and blood due to intake of sakekasu. In addition, there are no studies on changes in stool flora related to metabolites such as uremic substances and short-chain fatty acids among the previously reported studies on sake-kasu intake and stool flora, and there is a lack of data on evaluation indices to show the usefulness of sake-kasu intake.

Therefore, the purpose of this study is to evaluate changes in metabolites and bacterial flora in stools by amount and duration of sake-kasu intake in patients with chronic constipation without CKD. Based on the results obtained in this study, we will establish the amount and duration of sake lees intake in a small RCT of patients with CKD.

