**3. Scientific rationale and basis for the research**

**Study summary and primary endpoints**

The subjects of this study will be patients with chronic constipation and the intervention will be consumption of 25 g/day or 50 g/day of sake-kasu. The control will be pre-intervention, and the primary endpoint will be the percentage change in the concentration of uremic substances (indole and cresol) in the stool after 2, 4, and 6 weeks. The study design will be a single-arm (2-dose) pre/post comparison.

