**Validity of the study design**

The subjects of this study shall be patients with chronic constipation without CKD. So far, there are no studies using sakekasu for CKD patients as far as we could find, and there are a few studies on patients with chronic constipation. There have been reports of an increase in certain species of bacteria that are considered beneficial bacteria after consumption of sake lees,^7)^ and the effect of improving constipation,^8)^ . Since changes in the intestinal microbiota and uremic substances can be inferred from sake lees consumption, and these changes can be expected to be observed even in those without impaired renal function, patients with chronic constipation without CKD should be included in this study.

The intervention will be intake of 25 g/day or 50 g/day of sakekasu for 6 weeks. In previous reports, studies on subjects with constipation have reported improved intestinal microbiota after 4 weeks of intake of 190 g of amazake (equivalent to 25 g of sakekasu)^7)^ and the effect of 3 weeks of intake of 50 g of sakekasu on constipation^8)^ . In addition, a study of CKD patients reported a decrease in blood uremic substance levels after 6 weeks of synbiotic supplementation^10)^ . Based on these results, the intervention in this study will be the intake of 25 g/day or 50 g/day of sake-kasu for a total of 6 weeks, and based on the results obtained, the amount and duration of sake-kasu intake in a small RCT of CKD patients will be established.

The method of outcome evaluation will be a before-and-after comparative study with no comparators. This study is conducted to obtain the rationale for setting the amount and duration of sake lees intake in a small RCT of CKD patients. Since changes in uremic substances in stools can be confirmed by pre- and post-intervention comparisons, this is a single group (2 doses) pre- and post-comparison study without a comparison group. Evaluation will be conducted 4 times at intervention, 2 weeks, 4 weeks, and 6 weeks after the intervention, and the amount and duration of intake of sake lees in a small RCT will be set.

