**Sample Acquisition**

Samples will be obtained by the following methods a schedule of actions will be prepared separately for the participants, describing how and where the stool samples will be submitted, and will be explained to them at the time of obtaining their consent.

1. Stool samples are taken at intervention, 2, 4, and 6 weeks after sake lees consumption to obtain concentrations of uremic substances in stool, short-chain fatty acids, and bacterial flora in stool.
2. Urine samples at intervention and after 6 weeks to obtain urinary pH.
3. Stool and urine samples will be collected at the participant's home using the prescribed kit.
4. At intervention, 2, 4, and 6 weeks after sake lees consumption, blood samples are taken to obtain blood D-amino acid levels.
5. The examinee records the status of sake lees intake daily using an independently prepared record sheet (Appendix 2).
6. Daily recording of defecation frequency and stool characteristics by the examinee using the Bristol Scale^12)^ (Appendix 3).
7. Validated dietary assessment instruments will be administered 2 weeks prior to the intervention and at the end of the intervention (6 weeks later) to assess food intake frequency and nutrient intake.

*4 involves a minor invasion when collecting blood samples. 1, 2, 3, 5, and 6 do not involve physical invasion since they are obtained through stool and urine samples and questionnaires.

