**(2) Secondary endpoints**

- Percentage change in the percentage of major bacterial species in stool
- Concentration of short-chain fatty acids (acetic acid, lactic acid, propionic acid, butyric acid) in stool
- Stool pH, stool characteristics, frequency of defecation
- D-amino acid concentration in blood
- Defecation frequency and characteristics, constipation and quality of life score (PAC-QOL)
- Frequency of food intake, amount of nutrients consumed, and percentage of compliance with sake lees

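### A sake-lees breakfast is set for weeks 2, 4 and 6 but no breakfast for baseline, and blood-draw timing is unstated, so the change in blood D-amino acids could reflect that morning's meal

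*Protocol*

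**What the plan says.** Protocol section 6(2), Research Procedures, lists four evaluations in item 6: "Outcome items will be assessed at intervention, 2, 4, and 6 weeks". Item 10 standardises the evening before, without limiting it to follow-up visits: "The same dinner (a frozen home-delivered lunch with controlled nutritional value) on the day before the evaluation". Item 11 fixes the morning meal, but only after baseline: "Breakfast on the day of evaluation after 2, 4, and 6 weeks will be the same meal containing sakekasu".

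Under Sample Acquisition, item 4 reads: "At intervention, 2, 4, and 6 weeks after sake lees consumption, blood samples are taken to obtain blood D-amino acid levels". The Schedule of Observations and Inspections in section 7 likewise marks a blood test at the time of intervention and at weeks 2, 4 and 6. None of these places gives a fasting rule, a clock time or an interval between breakfast and draw.

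The Background in section 2 says that fermented foods such as sake lees contain D-amino acids and that "direct intake of D-amino acids from sake-kasu may provide renoprotective effects". Section 9(2) lists "D-amino acid concentration in blood" as a secondary endpoint, and section 7 names the analytes as D-serine and D-alanine. Section 3 says "The control will be pre-intervention" and "The method of outcome evaluation will be a before-and-after comparative study with no comparators".

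**The concern.** By the protocol's own account, the follow-up breakfast is a source of the class of substance being measured in blood. The baseline breakfast is left open. It cannot contain study sake lees, because the control is the pre-intervention value. It may contain other fermented foods, because item 9 allows ordinary foods such as miso and yogurt.

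If blood is drawn after breakfast, each comparison with baseline sets a morning with a fixed sake-lees meal against a morning with an unspecified meal. No group eats the same breakfast without the preceding weeks of intake, so no later analysis can separate the two contributions. What is at stake is the attribution of any rise in blood D-alanine or D-serine to sustained intake. These are secondary outcomes, but plasma D-alanine is in the title, and the Background presents the blood response to sake lees as something no study has examined.

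**Working it through.** The protocol has no calculated figure to reproduce: section 10 sets eight cases on feasibility, with no effect size, SD or power. The check is therefore a comparison of the visit rules, followed by an illustration.

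**1. Conditions by visit**

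| | Baseline | Weeks 2, 4, 6 |
|---|---|---|
| Dinner the evening before | Standardised (item 10) | Standardised (item 10) |
| Breakfast on the day | Not specified; no study sake lees | Same meal containing sake lees (item 11) |
| Blood for D-amino acids | Drawn | Drawn |
| Draw time relative to breakfast | Not stated | Not stated |

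Breakfast is the only one of these conditions that a stated rule makes different between baseline and follow-up.

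**2. What each contrast contains**

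Let S_k be the effect of sustained intake at week k, M the shift in blood level from the sake-lees breakfast, and B the shift from whatever was eaten on the baseline morning. Treat M as the same at each follow-up.

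- Blood drawn after breakfast: week k minus baseline = S_k + M − B.
- Blood drawn before breakfast at every visit: week k minus baseline = S_k, because M and B drop out.
- Week 6 minus week 2: (S_6 + M) − (S_2 + M) = S_6 − S_2. The meal cancels, and likewise for the other follow-up pairs.

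So the problem is confined to contrasts with baseline, and exists only if the draw follows breakfast.

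**3. Illustration of consequence, with assumed meal shifts**

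The protocol states analysis of variance with a two-tailed 5% Dunnett test for the primary stool endpoint only; it is borrowed here for the blood endpoint. Inputs: n = 8 and four visits (from the protocol); independent visit errors with SD 1, S_k = 0, B = 0 and a range of M (assumed).

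Test statistic: t_k = (mean_k − mean_0) / √(2·MSE/n), with residual df = (8 − 1)(4 − 1) = 21. The critical value for the largest of three |t_k| was obtained by simulation (40,000 runs) as 2.54. The noncentrality of each contrast is M·√(n/2) = M·√4 = 2M.

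| Assumed M (within-person visit SDs) | Noncentrality 2M | At least one contrast significant | All three significant |
|---|---|---|---|
| 0 | 0 | 5% (by construction) | – |
| 0.5 | 1 | 18% | 1% |
| 1.0 | 2 | 54% | 13% |
| 1.5 | 3 | 87% | 45% |
| 2.0 | 4 | 99% | 82% |

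A two-sided 5% paired t test at a single visit gives the same message. With n = 8, df = 7 and noncentrality d·√8, where d is the shift in SDs of the change, the rejection rate is 23% at d = 0.5, 68% at d = 1.0 and 95% at d = 1.5. If the eight were split four and four by dose and one dose were tested alone (n = 4), the figures are 11%, 29% and 53%.

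These figures do not estimate the bias. They show that a meal shift of about one within-person SD would be enough to matter.

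**The case against.** The strongest reply is that the confounding is conditional. A reader might infer from the fixed test-day breakfast that blood is drawn after it. The protocol does not say so, and a fasting draw at every visit would remove the problem. That stands, and it is why the point is worded as a possibility. It does not remove the need for a change, because the text as written permits the confounded draw.

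A second reply is that absorption from a serving is part of the question: the Background names direct intake as a route of interest, and the protocol never claims that the blood measure isolates a sustained effect. This is fair. A post-meal measure is legitimate if it is labelled as such, but the contrast then also needs a controlled baseline breakfast and a fixed interval to the draw.

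A third reply concerns reach. Sections 2 and 3 base the amount and duration for the later CKD trial on changes in stool metabolites and flora, and comparisons among weeks 2, 4 and 6 share the breakfast. A reader might infer that the choice of duration is compromised; the documents do not support that. Nor do they support an inference that the two dose groups receive equal sake lees at breakfast and the dose contrast is therefore blurred. The words about the same meal read naturally as the same across visits, and the portion by dose is not settled. Item 8's example of taking 25 g in one meal concerns ordinary intake and does not bound the breakfast portion.

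**Conclusion.** The point holds as a should-fix for one secondary endpoint. A stated rule makes the morning meal differ between baseline and follow-up, that meal contains the analyte class, and nothing fixes the draw relative to it. If blood is drawn after breakfast, the change from baseline in D-serine and D-alanine could partly or wholly reflect that morning's meal.

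The size cannot be derived from the protocol, which gives no D-alanine content, kinetics or SD. The rates shown above rest on assumed meal shifts, a true sustained effect of zero, and an analysis the protocol states only for the primary endpoint.

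A reader might infer that the blood endpoint would come out positive at every follow-up. That is not supported: in the illustration all three contrasts are significant in 1% of runs at 0.5 SD and 13% at 1 SD, reaching 82% only at 2 SDs. No effect on the primary stool indole and cresol endpoint is claimed.

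**What to change.** In section 6(2), under Research Procedures and Sample Acquisition, make the blood-draw conditions the same at all four visits: draw before breakfast after an overnight fast, with the sake-lees breakfast eaten afterwards at weeks 2, 4 and 6. This removes that morning's meal from every contrast with baseline.

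If a post-meal sample is intended, serve the same breakfast without sake lees at baseline, fix the interval from meal to draw at all visits, and report the blood result as including an acute meal effect. This controls the rest of the meal but does not separate acute absorption from sustained intake, so the labelling is essential.

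The cost is small: participants attend fasting on four mornings, or one more standardised breakfast is provided. No extra samples are needed and the target of eight is unchanged.
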